### 12-Lead Electrocardiogram

12-lead ECG recordings will be obtained according to the schedule of assessments prior to dosing, if applicable (see section 6.5). The following ECG parameters will be recorded: heart rate, RR interval, PR interval, QRS complex interval and QT interval. In addition, QTc will be calculated using the Bazett and Fridericia formula by the Data Management department of PSI. A clinical assessment of “Normal”, “Abnormal, not clinically significant” or “Abnormal, clinically significant” will be made.

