## Non-clinical data

The NOAEL observed in rats following 28 days dosing was set at 17.5 mg/kg, the highest dose tested in toxicology studies. In all animals, a significant increase was observed in serum protein, serum globulin, and in spleen size and weight, consistent with the development of an antibody response against DC-TAB.

A study was conducted in beagle dogs who received DC-TAB in doses up to 5 mg/kg. After approximately 8-10 consecutive days of intravenous DC-TAB administration, treatment-related clinical symptoms started to develop immediately after administration in all treatment groups except for the male dogs receiving 0.5 mg/kg which all remained symptom-free. Clinical symptoms included pallor of otherwise well-perfused tissues such as the tongue and membranes in eyes and mouth, often preceded by brief reddening. More severe clinical signs included lethargy, spasms, abnormal posture and gait, and abnormal breathing. In a few cases, mild secretory symptoms or pallor already developed after 5-6 days. All the above clinical symptoms reversed within minutes after DC-TAB administration. Only a weak correlation was observed between the severity of clinical signs and the DC-TAB dose administered. In line with the findings in the above range-finding and maximum tolerated dose (MTD) studies, females tended to develop slightly more severe signs than males. In a rather abrupt reversal, all of these clinical signs stopped appearing after 12-14 days of treatment in almost all cases.

All pre-clinical data in dogs, the more sensitive species, indicate that there is a crucial difference between DC-TAB administration in naïve animals as compared to animals that had received DC-TAB before. Upon repeated administration, and with a minimum time interval of five days between a first and consecutive dose(s), significant clinical symptoms emerge immediately upon administration of such a consecutive dose, even a low dose. In naïve animals on the other hand, up to five consecutive doses of 12 mg/kg DC-TAB did not trigger any adverse effects.

The data do not allow formal definition of a NOAEL in female dogs following 15 days administration. In male dogs, the NOAEL is 0.5 mg/kg following 15 days administration. In naïve female and male dogs, the NOAEL up to five consecutive doses is 12 mg/kg.

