## Clinical data

A phase I, placebo-controlled, double-blind clinical study on the safety, tolerability, pharmacokinetics and T-cell tolerizing effect of DC-TAB in healthy volunteers has been finalized. In this study, the effects have been examined of single i.v. dosing (using 4, 12.5, 25 and 37.5 mg doses) in a first part of the study, and three consecutive daily i.v. doses of DC-TAB (using 10, 25 and 37.5 mg doses) in a second.

Single dose, bolus administration of DC-TAB up to 37.5 mg was well tolerated and safe. In addition, daily dosing of up to 37.5 mg for three consecutive days was well tolerated and safe in healthy volunteers. Following multiple dosing of high concentrations DC-TAB, mild to moderate injection site reactions were observed. The incidence of these reactions was lower when the concentration of DC-TAB in the bolus injections was lowered.

No changes were detected in serum antibody levels against CRYAB over a 28-day period following any of the treatment regimens.

Pharmacokinetic parameters indicate that serum levels of DC-TAB decrease with a half-life of around 60-75 min at all doses tested.

Immunological data indicate a statistically significant reduction in both CD4+ and CD8+ memory (CD45RO^+^) T-cell responses against CRYAB following a single dose level of 12.5 mg, becoming apparent already within 8 days after i.v. administration of DC-TAB. This effect was maintained for at least 28 days. In half of the subjects, the T-cell responses to CRYAB were suppressed to levels considered to reflect non-responsiveness. Antigen-specific T-cell responsiveness (partially) recovers 6-8 months after treatment. These findings are consistent with the notion that i.v. administration of DC-TAB induces antigen-specific inducible regulatory FoxP3+ T cells (iTregs), which functionally suppress the response by other T cells. Consistent with what is known on the dynamics of such a response, the suppressive effect was found to be partially lost after 6-8 months.

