## Schedule of assessments

Table 6‑1 Schedule of assessments

| **Assessment** | **Week -4 to -1 (screening)** | **Day 0** | **Week 1**  **± 1 d** | **Week 2**  **±1 d** | **Week 4**  **± 3 d** | **Week 8**  **± 3 d** | **Week 12**  **± 3 d** | **Week 16**  **± 3 d** | **Week 20**  **± 3 d** | **Week 24 or EoT**  **± 3 d** | **Week 36**  **± 3 d** | **Week 48**  **± 3 d** |
| --- | --- | --- | --- | --- | --- | --- | --- | --- | --- | --- | --- | --- |
| Written consent | x |  |  |  |  |  |  |  |  |  |  |  |
| Inclusion/Exclusion criteria | x |  |  |  |  |  |  |  |  |  |  |  |
| Demographic data | x |  |  |  |  |  |  |  |  |  |  |  |
| Medical History | x |  |  |  |  |  |  |  |  |  |  |  |
| Previous medication | x |  |  |  |  |  |  |  |  |  |  |  |
| Study drug administration^4^ |  | x |  |  |  | x |  | x |  |  |  |  |
| MRI | x |  |  | x | x | x^3^ | x | x^3^ | x | x | x | x |
| EDSS | x | x |  |  |  | x |  | x |  | x | x | x |
| MSIS-29 |  | x |  |  |  | x |  | x |  | x | x | x |
| Neurological evaluation/clinical relapse | x | x | x | x | x | x | x | x | x | x | x | x |
| Blood sample for effect parameters (T-cell response | x | x |  |  | x | x | x | x | x | x | x | x |
| Anti-CRYAB/DC-TAB antibodies | x | x |  |  | x | x | x | x | x | x | x | x |
| Safety Laboratory Tests (Haematology, Biochemistry, Urinalysis) ^6^ | x | x | x |  | x | x |  | x |  | x | x | x |
| Urine Pregnancy Test | x |  |  |  |  | x |  | x |  | x |  |  |
| PK sampling | x^8^ | X^1^ |  |  |  |  |  |  |  |  |  |  |
| Physical examination | x | x | x | x^2^ | x^2^ | x | x^2^ | x | x^2^ | x | x^2^ | x |
| Vital Signs ^7^ | x | x |  |  |  | x |  | x |  | x |  | x |
| Body temperature^7^ | x | x |  |  |  | x |  | x |  |  |  |  |
| 12-Lead ECG | x | x |  |  |  | x |  | x |  | x |  | x |
| Adverse events |  | X^5^ | x | x | x | x^5^ | x | x^5^ | x | x | x | x |
| Concomitant medication |  | x | x | x | x | x | x | x | x | x | x | x |

^1^ Samples (relative to study drug administration) at pre-dose, t=10 minutes, t=20 minutes, t=30 minutes, t=1 hour, t=2 hours, t=4 hours, t=8 hours, t=16 hours, t=24 hours;

^2^ Brief physical examination (symptom guided)

^3^ MRI can be made on dosing days after study drug administration

^4^ On study drug administration visits need patient hospitalization for 24h after dosing.

^5^ Repeated adverse event review is needed 24 hours after each dosing

^6^ See the full list of the laboratory parameters in section 7.2.1.

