^7^ On dosing days blood pressure, pulse rate and temperature will be measured before and 1 hour after dosing; respiration rate only pre-dose.

All assessments are to be done prior to study drug administration unless otherwise stated.

^8^ Ten patients only; one sample collected to further investigate the stability of blood samples

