### Vital Signs

Blood pressure (systolic (SBP) and diastolic (DBP)), pulse rate and respiration rate after 10 minutes supine rest will be recorded on each dosing days and at weeks 36 and 48. On dosing days, evaluations will be done pre-dose and, in addition, blood pressure and pulse rate will be assessed at 1 hour after dosing. Automatic or manual devices may be used. All devices must have been calibrated in the previous 12 months. Calibration certificates must be available on request.

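### On dosing days no ECG or respiration rate follows the injection and other vital signs are read once, at 1 hour, so the measured safety data cannot register a minutes-long re-exposure reaction

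*Protocol*

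**What the plan says.** **ECG.** Section 7.2.6 states that "12-lead ECG recordings will be obtained according to the schedule of assessments prior to dosing, if applicable". The general note under Table 6-1 points the same way: "All assessments are to be done prior to study drug administration unless otherwise stated". No exception is made for ECG. Table 6-1 places ECGs at screening, day 0 and weeks 8, 16, 24 and 48. Doses are given at day 0 and weeks 8 and 16.

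**Vital signs.** Footnote 7 to Table 6-1 reads: "On dosing days blood pressure, pulse rate and temperature will be measured before and 1 hour after dosing; respiration rate only pre-dose". Section 7.2.4 agrees on dosing days ("in addition, blood pressure and pulse rate will be assessed at 1 hour after dosing"), and section 7.2.5 sets the same times for temperature. For the other visits, section 7.2.4 says that vital signs "will be recorded on each dosing days and at weeks 36 and 48", whereas Table 6-1 marks weeks 24 and 48 and leaves week 36 blank.

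**What is known about re-exposure.** Section 1.4 reports that dogs given a further dose at least five days after the first developed significant signs immediately, even at a low dose. Abnormal breathing was among the more severe signs in dogs, and "All the above clinical symptoms reversed within minutes after DC-TAB administration". Section 1.5 reports that in humans "serum levels of DC-TAB decrease with a half-life of around 60-75 min at all doses tested".

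**Analysis.** ECG and vital signs are listed safety parameters (section 10.1.1) under a primary objective of safety and tolerability (section 3.1). The synopsis plans descriptive summaries and changes from baseline for both, and shift tables for ECG.

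**The concern.** The protocol presents the safety of dosing again after 2 months as an open question. Section 1.6.1 lists it among the things the trial has to establish, and section 1.6.2 says that the effect of the longer interval is not yet known. The Phase I study described in section 1.5 gave single doses or three doses on consecutive days, so it did not test an interval of five days or more.

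The one re-exposure reaction that the protocol describes is immediate and short, and breathing is among the functions affected. Yet respiration rate is the one vital sign expressly left out after the injection, ECG is left out as well, and the remaining readings come an hour later. The ECG and respiration summaries will then contain no value taken in the hours after a dose. An unremarkable table could be read as reassurance about acute effects on which it holds no information.

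**Working it through.** No sample-size or power figure is at stake; section 10.5 says that the number of patients has no statistical basis. The check sets measurement times against dose times.

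**Inputs.** Doses at weeks 0, 8 and 16; post-baseline ECGs at weeks 8, 16, 24 and 48 (Table 6-1), those on dosing days being pre-dose; serum half-life 60 to 75 min (section 1.5); four arms of 8, so 24 patients on active drug (synopsis).

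**1. Nominal time from the preceding dose to each post-baseline ECG**

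| ECG visit | Preceding dose | Gap |
| --- | --- | --- |
| Week 8 (pre-dose) | Week 0 | 8 - 0 = 8 weeks |
| Week 16 (pre-dose) | Week 8 | 16 - 8 = 8 weeks |
| Week 24 | Week 16 | 24 - 16 = 8 weeks |
| Week 48 | Week 16 | 48 - 16 = 32 weeks |

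The shortest gap is 8 weeks = 56 x 24 x 60 = 80,640 min. That is 80,640 / 75 = 1,075 to 80,640 / 60 = 1,344 half-lives, so no planned post-baseline ECG is taken with drug in serum. ECGs after the injection on a dosing day: 0 of 3. Respiration rates after the injection on a dosing day: 0 of 3.

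**2. Re-exposure injections without these readings.** 24 active patients x 2 repeat doses = 48 injections (32 x 2 = 64 with placebo). Same-day post-dose ECGs or respiration rates for them: 0.

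**3. What the 1-hour reading can show.** Share of drug left at 60 min = 0.5^(60 / half-life):

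- half-life 60 min: 0.5^1 = 50%
- half-life 75 min: 0.5^0.8 = 57%

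Blood pressure, pulse and temperature at 1 hour are therefore read while drug is present and can show an effect that lasts that long. They cannot show one that is already over. Section 1.4 says only that the signs cleared within minutes. With assumed durations of 5, 10 or 30 min from injection, the reaction has ended before the 60-min reading in each case.

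**4. Non-dosing vital-sign visits.** Section 7.2.4 gives weeks 36 and 48; Table 6-1 gives weeks 24 and 48. The primary analysis covers the 24-week treatment period. Under section 7.2.4 the last vital signs in that period would be those at the week 16 dose; under Table 6-1 there is a reading at week 24.

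**The case against.** **Adverse events remain a route of detection.** Patients stay in hospital for 24 hours after each dose (section 6.2), adverse events are reviewed again at 24 hours (Table 6-1, footnote 5), and systemic reactions must be recorded (section 7.2.7). Adverse events are the first safety parameter listed in section 10.1.1. The dog signs (pallor, lethargy, spasms, abnormal posture, gait and breathing) are visible at the bedside. This stands. A reader might infer that the trial's safety evaluation would miss such a reaction altogether; the protocol does not support that. The loss is of measured values collected in the same way in every arm.

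**ECGs are taken after dosing.** A reader might also infer that ECG and respiration rate are never recorded once treatment has begun. That is wrong: ECGs follow at weeks 8, 16, 24 and 48, and vital signs are taken at later visits. The gap lies on the dosing day, after the injection.

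**Relevance to humans is unproven.** Section 1.2 says that dogs lack the natural immune reactivity to the protein that adult humans have. Section 1.4 reports no toxicologically significant cardiovascular, respiratory or neurobehavioural effect in safety pharmacology studies up to 17.5 mg/kg, and describes no ECG sign in the dog reaction. Section 1.5 reports no antibody rise over 28 days in Phase I. All this stands, with one limit: the protocol does not say that the safety-pharmacology animals had been dosed before, and it calls prior exposure the crucial difference. The dog data therefore bear most directly on respiration and early vital signs. The case for an ECG rests on its being a listed safety parameter with no reading during exposure.

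**Safety laboratory tests.** One might extend the point to the longer gap in laboratory tests after doses 2 and 3. Laboratory timing has no bearing on a reaction that lasts minutes, and the protocol cites no laboratory signal that would carry the extension.

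**Conclusion.** The point holds for dosing-day measurement. On all three dosing days, no ECG and no respiration rate follows the injection, and blood pressure, pulse and temperature are read once, at 1 hour. The earliest ECG after a dose is nominally 8 weeks later, so the planned ECG change-from-baseline and shift tables cannot inform on acute effects. The measured vital signs cannot register a reaction that begins at injection and ends within minutes, at any of the 48 active re-exposure injections. The 1-hour readings do fall within exposure (about 50 to 57% of drug remaining) and keep some value for longer-lasting effects.

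This rests on reading section 7.2.6 and the pre-dose default in Table 6-1 as written, on the Phase I half-life applying to patients, and on taking minutes to mean less than an hour. It does not rest on the dog reaction occurring in humans, which is uncertain; the protocol itself leaves the safety of 2-month re-dosing open. The conflict over non-dosing vital-sign visits is a separate, smaller contradiction and is certain.

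**What to change.** Reconcile the measurement times in Table 6-1, its footnote 7 and sections 7.2.4 and 7.2.6 with what sections 1.4, 1.6.1 and 1.6.2 say about re-exposure. As measurements for the safety parameters, on each of the three dosing days and in all arms:

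- keep the pre-dose readings as reference;
- add a vital-signs set that includes respiration rate soon after the injection;
- add respiration rate to the existing 1-hour set;
- add one ECG after the injection on the same day, while drug is still present. Taken with the 1-hour set, it would cover exposure but not a reaction lasting minutes, and the report should say so.

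State in the analysis text that ECGs taken 8 weeks or more after a dose describe late, not acute, effects. Make section 7.2.4 and Table 6-1 agree on the non-dosing vital-sign visits.

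The cost is three ECGs and a few extra readings per patient, all within the hospital stay already planned. No visit is added.

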### Adverse Events including local and systemic reactions

The investigator is responsible for recording all AEs, including any local and systemic reactions, observed during the study. Persisting reactions should be evaluated by the investigator and the investigational product could be discontinued if indicated. See section 11.2 for detailed information on AE collection.

### Concomitant medication/antidotes

The investigator should record the use of all concomitant medications, both prescribed and over-the-counter, on the CRF. This includes drugs used on a chronic and as-needed basis. The following will be recorded on the CRF: Drug name (trade name), total daily dose, route, start and end date and time, whether ongoing and indication.

All concomitant medication will be coded using the World Health Organization’s Drug Dictionary (WHO-DD).

## Pharmacokinetics

4 mL blood samples will be taken for assessment of serum concentrations levels of DC-TAB at pre-dose, t=10 minutes, t=20 minutes, t=30 minutes, t=1 hour, t=2 hours, t=4 hours, t=8 hours, t=16 hours and t=24 hours relative to dosing on day 1. Within 2 hours after blood sampling, blood will be centrifuged at 2,000 g for 20 minutes at 4°C. In case a cooled centrifuge is not available, the rotor heads or the centrifuge may be cooled to around 4°C prior to centrifuging. Immediately after centrifugation, serum will be stored in two labelled polypropylene tubes at ≤ -20°C for serum concentration analysis. All serum concentration analyses will be performed according to GLP after the study has been finalized.

DC-TAB in serum samples, stored frozen at -20°C, has been examined for structural stability by informal non-GLP studies, using detectability by a monoclonal antibody in a sandwich ELISA as parameters for integrity. DC-TAB was found to be fully stable under such conditions for a period of at least 6 months.

In ten patients a sample will also be collected at baseline to further investigate the stability of the samples.

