# Treatments

## Treatments administered

The pharmacy or an unblinded nurse not involved in clinical conduct of the study will prepare all study medication for all patients according to the treatment randomization list.

Patients will receive a single dose of study medication as intravenous bolus injection administered in the arm every two months, for a total of three times during the study. The required amount of study medication will be administered over 30 seconds to the patient via an intravenous catheter.

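### With the first PK draw 10 minutes after a 30-second bolus, observed Cmax is about 8-10% low and tmax only reflects the schedule, while the 16-hour draw adds little

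*Protocol*

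**What the plan says.** Protocol Section 5.1 says the dose "will be administered over 30 seconds to the patient via an intravenous catheter".

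Section 1.5, on the healthy-volunteer Phase I study, reports that "serum levels of DC-TAB decrease with a half-life of around 60-75 min at all doses tested".

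Section 7.3 sets the PK samples "at pre-dose, t=10 minutes, t=20 minutes, t=30 minutes, t=1 hour", then at 2 and 4 hours, and finally at "t=8 hours, t=16 hours and t=24 hours relative to dosing on day 1". Footnote 1 of Table 6-1 (Section 6.5) gives the same times. That makes nine post-dose draws of 4 mL each. Section 6.2 and Table 6-1 place them on the first dosing day only.

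Section 10.1.3 lists AUC0-24h, AUC0-∞, Cmax, t1/2, tmax and Kel as the PK parameters. Section 10.3.3 puts AUC and Cmax into an analysis of variance, with and without log transformation, and leaves further detail to the statistical analysis plan. PK in patients is a secondary objective (Section 3.2).

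The protocol gives no reason for the 16-hour draw or for the lack of a draw before 10 minutes. It states no lower limit of quantification.

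**The concern.** After a 30-second intravenous injection, the serum level should peak at or just after the end of injection and then fall. With nothing sampled before 10 minutes, the highest measured value is the 10-minute value. Two named parameters are affected: Cmax is low in every patient, and tmax merely records the time of the first sample.

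Meanwhile one of the nine draws is taken at 16 hours, when the protocol's own half-life leaves almost nothing to measure. Full profiles are taken at the first dose only, so a later occasion cannot fill the early gap. No analysis plan can restore blood that was not drawn.

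**Working it through.** The protocol states no derived PK figure on this point, so there is none to reproduce.

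**Inputs.** Half-life T = 60 to 75 min (Section 1.5); injection time 0.5 min (Section 5.1); sampling times (Section 7.3; Table 6-1, footnote 1). One-phase decline is assumed unless stated otherwise.

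**Level left at each draw**, 2^(-t/T), for the two ends of the half-life range:

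| Draw | Half-lives elapsed | Level left, % of initial |
|---|---|---|
| 10 min | 0.13-0.17 | 89.1-91.2 |
| 8 h | 6.4-8 | 0.39-1.18 |
| 16 h | 12.8-16 | 0.0015-0.014 |
| 24 h | 19.2-24 | 0.000006-0.00017 |

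**Cmax.** Timing from the start of injection, the 10-minute level relative to the end-of-injection peak is 2^(-(10-0.5)/T).
- T = 60: 2^(-9.5/60) = 0.896, so Cmax is 10.4% low.
- T = 75: 2^(-9.5/75) = 0.916, so Cmax is 8.4% low.

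Timed from the end of injection, or against an instantaneous-bolus C0, the ratios are 0.891 and 0.912, so 8.8-10.9% low.

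**AUC before the first draw.** The share is 1 - 2^(-10/T) = 10.9% (T = 60) or 8.8% (T = 75). Under the same model it can be recovered. With T = 60 the levels at 10 and 20 min are 0.891 and 0.794 of C0, and log-linear back-extrapolation gives 0.891²/0.794 = 1.00. With T = 75 it is 0.912²/0.831 = 1.00.

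**AUC at the late end.** The share beyond 8 h is 0.39-1.18%, and beyond 16 h it is 0.0015-0.014%. AUC0-24h and AUC0-∞ differ by less than 0.0002%.

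**Sensitivity to a fast early phase (assumed, not in the documents).** Let it carry a fraction f = 0.3-0.5 of C0 with half-life a = 3-10 min. The 10-minute level is f·2^(-10/a) + (1-f)·2^(-10/T).
- Mildest case: f = 0.3, a = 10, T = 75 gives 0.3×0.5 + 0.7×0.912 = 0.788.
- Most severe case: f = 0.5, a = 3, T = 60 gives 0.5×0.099 + 0.5×0.891 = 0.495.

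Cmax would then be 21-50% low. A phase largely over by 10 minutes could not be seen with this schedule.

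**Sensitivity to a slow late phase (also assumed).** A component of 1% of C0 with an 8-hour half-life leaves 0.01×2^(-2) = 0.25% at 16 h and 0.01×2^(-3) = 0.13% at 24 h.

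**Effect of an early draw.** At 5 min after the end of injection the level is 2^(-5/60) = 0.944 or 2^(-5/75) = 0.955 of peak, a shortfall of 4.5-5.6% in place of 8.4-10.4%.

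**The case against.** The schedule contradicts nothing. Section 7.3 and Table 6-1 agree, and every listed parameter can be computed from it. The half-life comes from healthy volunteers and this is the first study in patients, so late draws have a purpose: they are where an unexpected slow phase would show. No lower limit of quantification is given, so it cannot be proved that the 16-hour sample would be unmeasurable. PK is secondary, the serum assays are run after the study has ended, and no dose or stopping rule in the protocol uses Cmax. An early draw has its own weakness: at a few minutes, timing error and incomplete mixing matter more, and Section 8.4 flushes the injection catheter with 10 ml of buffer. All of this stands, and it keeps the point minor.

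Three stronger readings are tempting, and the documents do not support them.
- A reader might infer that the 16-hour and 24-hour draws are both wasted. The 24-hour draw closes AUC0-24h, which is a named parameter, and can reveal a slow phase.
- A reader might infer that AUC is biased by 9-11%. That share lies before the first sample but can be back-extrapolated under the one-phase model that yields it. The method of calculation may be left to the statistical analysis plan.
- A reader might infer that the dose comparison is compromised. Under linear kinetics the same proportion is lost at 7.5, 12.5 and 17.5 mg, so ratios of Cmax between doses are largely unchanged.

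The objection does not remove the understated Cmax or the uninformative tmax, because both follow from where the first sample lies.

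**Conclusion.** The point holds, as a minor one. Observed Cmax will be about 8-10% below the end-of-injection peak, and tmax will be 10 minutes in essentially every patient. The 16-hour draw adds little beyond those at 8 and 24 hours.

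The size rests on three assumptions: that the Phase I half-life applies to patients, that decline is one-phase, and that the level falls from the end of injection. The direction of the Cmax bias does not depend on the exact half-life. The 21-50% range is illustrative only, since the documents report a single half-life and no distribution phase. The primary safety objective is not affected.

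**What to change.** In Section 7.3 and in footnote 1 of Table 6-1:
- Move the 16-hour draw to about 5 minutes after the end of injection. Say whether times run from the start or the end of injection, record the actual time, and take the sample away from the flushed injection catheter.
- Keep the 24-hour draw, for AUC0-24h and as a check for a slow phase.

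In the reporting, give the back-extrapolated C0 beside observed Cmax, and do not interpret tmax.

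**Cost.** The number of draws, the blood volume and the number of assays stay the same, and patients are in hospital for 24 hours after dosing anyway. There are three downsides:
- A slow terminal phase would rest on one point after 8 hours.
- The early sample is more sensitive to timing and mixing.
- The wider gap from 8 to 24 hours makes a linear trapezoid coarser. With AUC = T/ln 2 (86.6 or 108.2 min × C0), a straight line from the 8-hour level to about zero at 24 h gives 0.5×960×0.0039/86.6 = 2.2% of AUC (T = 60) or 0.5×960×0.0118/108.2 = 5.2% (T = 75), against true shares of 0.4% and 1.2%. A log-linear rule on the declining part, or extrapolation from 8 hours if the 24-hour sample is not quantifiable, avoids this.
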